## Aim

### Primary

The main objective is to evaluate the effectiveness of the complex intervention MULTIPAP Plus, in improving prescriptions to a young-old population (65–74 years) with multimorbidity and polypharmacy measured with a composite endpoint of hospital admission or death at 18 months, compared with usual care.

### Secondary

To evaluate the effectiveness of MULTIPAP Plus, measured as hospitalizations and/or all-cause mortality compared to those for routine practice at 12 months, as well as drug safety, use of services, quality of life of the patient measured with the EQ-5D-5L, disability, number of fractures, and adherence to treatment.To study the cost-utility ratio for the intervention compared to usual care.To describe the usability, adherence, and satisfaction with the DSS CheckTheMeds®.

## Methods

### Design

Pragmatic parallel two-arm, superiority, community-based cluster-randomized controlled clinical trial with a follow-up of 18 months. The unit of randomization is the FP, and the unit of analysis is the patient. The cost-utility study will be carried out from the perspective of the Spanish National Health System with a time horizon of 2 years.

CONSERVE-SPIRIT has been used for reporting trial protocol instead of SPIRIT since MULTIPAP Plus had been suspended because of COVID-19 from March 2020 to May 2021 and methodologic modifications were made (Additional file 1: CONSERVE-SPIRIT checklist; Additional file 2: SPIRIT Trial Modifications in Extenuating Circumstance). This situation has been notified and updated in the trial registry.

### Scope of study

The scope of study is primary care within the Spanish National Health System. The Spanish National Health System provides first contact, comprehensive, continuous, coordinated care (which is free at the point of care) to define a population served by primary care centres. Patients have named family physicians who are responsible for delivering and coordinating their care.

### Study population

The study population includes patients between 65 and 74 years with multimorbidity and polypharmacy attending in primary care health centres in three autonomous communities Aragón, Madrid, and Andalusia.

*FPs inclusion criteria:*
Stable work situation, without intention to leave the position during the study.Agree to participate and sign the informed consent form

*Patient selection criteria:*

Inclusion criteria:
Age: 65–74 yearsMultimorbidity: ≥ 3 chronic diseasesPolypharmacy: ≥ 5 drugs prescribed for at least three months prior to inclusion in the studyHaving visited/contacted their family physician at least once in the last yearAble to follow the requirements of the studyAgree to participate and sign the informed consent form

Exclusion criteria:
Institutionalized patientsLife expectancy of less than 12 months based on their doctorPhysical or mental illness that in the opinion of their doctor does not allow them to follow the study requirements.

### Sample size

It was calculated under the hypothesis that the intervention would result in a difference of at least six percentage points in the combined variable (hospitalizations and/or all-cause mortality) between the study groups. According to previous studies, in the age range of 65 to 75 years, the criterion incidence of the estimated primary outcome variable was 16% [23, 34]. Considering a power of 80%, an alpha error of 5% and assuming simple random sampling, the required sample size would be 984 patients (492 patients per group).

The appropriate sample size for this type of design depends on the average size of the cluster and the degree of correlation between the individuals in the cluster. Consequently, it is necessary to adjust the sample size calculated according to the design effect (DE). An average group size of eight patients per FP and an intraclass correlation coefficient of 0.02 [35] produces the following (DE = 1 + (5–1) × 0.02 = 1.08), giving a sample size, corrected for design effect, of 1063 patients. Assuming a loss rate of 8%, the final sample size required is 1148 patients (574 per group).

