**Sample size:**

*n* = 1148 patients (574 per study arm).

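### The sample size section states eight patients per family physician but computes the design effect with five, so 1148 patients give either about 78% or about 80% power, depending on which figure is meant

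*Protocol article*

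**What the plan says.** The Sample size section of the protocol article builds the number in three steps.

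- **Individual-level size.** The target is "a difference of at least six percentage points in the combined variable" and, for patients of this age, "the criterion incidence of the estimated primary outcome variable was 16" per cent. The section continues "Considering a power of 80%, an alpha error of 5% and assuming simple random sampling" and concludes that "the required sample size would be 984 patients (492 patients per group").
- **Clustering.** It then gives "eight patients per FP and an intraclass correlation coefficient of 0.02 [35] produces the following (DE = 1 + (5–1) × 0.02 = 1.08"), which leads to a corrected size of 1063.
- **Loss.** "Assuming a loss rate of 8%, the final sample size required is 1148 patients (574 per group"). The operation behind this step is not written out.

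The Abstract repeats the result as "1148 patients (574 per study arm").

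**The concern.** The clustering sentence contradicts itself. Its words give a mean cluster of eight and its formula uses five. The figure inside the formula is the one that carries through to 1063 and to the headline 1148.

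Two planning quantities are therefore uncertain. One is the power: if eight is the plan, the design effect is understated and 1148 patients fall short of the stated 80%. The other is the number of clusters. The family physician is the unit of randomization, and the two readings imply quite different numbers of physicians for the same 1148 patients.

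The loss step adds a smaller question, since 1148 looks like a multiplication by 1.08 where a division by 0.92 is needed.

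**Working it through.** **Inputs, all from the Sample size section:** incidence 16%, difference 6 points, alpha 5%, power 80%, ICC 0.02, cluster size eight (words) or five (formula), loss 8%. Two assumptions are mine: a two-sided test, and a reduction from 16% to 10%. Together they reproduce the stated 492 per group. A one-sided test gives 388, and 16% versus 22% gives 670.

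**1. Reproducing the individual-level size.** With p̄ = (0.16 + 0.10)/2 = 0.13, the pooled two-proportion formula without continuity correction is

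n = [1.960 × √(2 × 0.13 × 0.87) + 0.842 × √(0.16 × 0.84 + 0.10 × 0.90)]² / 0.06² = 491.99,

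so 492 per group and 984 in total. This matches.

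**2. Reproducing 1063 and 1148.**
- DE = 1 + (5 − 1) × 0.02 = 1.08
- 984 × 1.08 = 1062.7, so 1063
- 1063 × 1.08 = 1148.04, so 1148

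The printed total is reproduced only with cluster size five and loss applied as × 1.08.

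**3. The same chain with the stated eight.**
- DE = 1 + (8 − 1) × 0.02 = 1.14
- 984 × 1.14 = 1121.8, so 1122
- 1122/0.92 = 1219.6, so 1220 (610 per group)

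This is 72 more than 1148 (72/1148 = 6.3%).

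**4. Separating the two slips.** With five and the correct loss step, 1063/0.92 = 1155.4, so 1156, which is 8 more than 1148. The loss step therefore accounts for 8 of the 72 patients and the cluster size for the other 64.

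**5. Power of 1148 patients for 16% versus 10%.** After 8% loss, 1148 × 0.92 = 1056 are analysed. The effective number per arm is 1148 × 0.92/(2 × DE).

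| Cluster size | DE | Effective n per arm | Power |
|---|---|---|---|
| 8 | 1.14 | 463 | 77.6% |
| 8, reduced by loss to 7.36 | 1.127 | 468 | 78.0% |
| 5 | 1.08 | 489 | 79.8% |
| 5, reduced by loss to 4.6 | 1.072 | 493 | 80.0% |

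At 463 per arm and a 16% control rate, 80% power needs a difference of about 6.2 points.

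**6. Number of family physicians.** 1148/8 = 143.5, so about 144. 1148/5 = 229.6, so about 230. The gap is about 86 physicians.

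**7. Whether the article settles it elsewhere.** The Recruitment section mentions 120 physicians from the earlier project plus an unstated number of others. The Discussion mentions over 130 health centres. Neither gives a total number of physicians, so both readings remain possible.

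**The case against.** A reader might infer that the trial is underpowered, or that 1148 patients cannot deliver 80% power. The article does not support that as a flat statement. It holds only if eight is the planned size and the five in the formula is the slip. Every number in the chain follows from five, while eight appears once, as a word. On the five reading the power is 79.8% to 80.0%, which is the stated figure for practical purposes. This part of the objection stands.

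A reader might also make much of the loss step. The × 1.08 is inferred from the result, although it matches exactly. By itself it costs 8 patients and about 0.2 points of power, so it deserves only a note.

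Finally, even on the eight reading the shortfall is about two points, no more than ordinary uncertainty in the inputs would cause. With clusters of eight and 8% loss, power is 80.1% at an ICC of 0.01 and 75.1% at 0.03. It is also 80.3% if the control rate is 15% with the same 6-point difference. That limits the consequence, and it is why the point asks for a correction of the text and not for a larger trial. It does not remove the contradiction: the two cluster sizes cannot both be right, and one printed planning figure has to change.

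**Conclusion.** The section is wrong as written. It states eight patients per physician and computes with five, and nothing else in the article reconciles the two.

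- **If eight is the plan,** the design effect is 1.14, the size for 80% power is 1220, and 1148 gives 77.6% (78.0% with the post-loss cluster size).
- **If five is the plan,** the power statement stands at 79.8% to 80.0%, but the stated cluster size is wrong and about 230 physicians are needed rather than about 144.

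These figures rest on a two-sided test, a reduction from 16% to 10%, the stated ICC of 0.02 and the stated 8% loss. The importance is that of a misstated planning figure. At most about two points of power are involved, and neither the conduct nor the analysis of the trial is affected by the slip itself.

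**What to change.** State which cluster size was planned, and make the words and the formula agree.

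- **If eight:** write DE = 1 + (8 − 1) × 0.02 = 1.14, keep 1148 patients, and restate the power as about 78% for 16% versus 10%, or as 80% for a difference of about 6.2 points.
- **If five:** correct the word eight and state the number of family physicians it implies, about 230.

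In either case, show the loss allowance as a division by 0.92. For the five-patient chain this is 1063/0.92 = 1156, and the text can note that 1148 is 8 below it.

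The cost is a wording correction in the Sample size section. On the eight reading the stated power also becomes slightly less favourable. No additional patients are needed.

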### Recruitment

MULTIPAP Plus has a group of 120 FPs who previously participated in the MULTIPAP project; voluntary participation has been proposed to this group and another FPs working in PC health centres in Aragón, Madrid, and Andalusia. Strategies to improve protocol adherence of FP will be considered (e.g. individual follow-up of protocol’s achievements and recognition via e-mail, offer to participate as co-authors in scientific papers, certified training sessions).

Patients will be selected by random sampling from the list of patients who meet the inclusion criteria. Subsequently, each FP will invite the listed patients, when the patient agrees to participate, the FP will inform them in detail about the study and confirm the inclusion/exclusion criteria and obtain the patient’s written informed consent. If they do not agree to participate, data on the patient’s age, sex, and reason for nonparticipation will be collected (see Fig. 1, flowchart).

**Fig. 1 Fig1:**
[figure not shown]
Flow diagram of patients

The selection of professionals was carried out in the third quarter of 2019. The recruitment of patients began in November 2019 and was suspended in March 2020. Considering the epidemiological situation in Spain, and the reorganization of health services including primary care, it was not possible to restart the study until May 2021. In that month, the situation of the family physicians was reviewed, and the commitment was updated, as well as the situation of the patients recruited between November 2019 and February 2020.

### Randomization

The unit of randomization is the FP, and the unit of analysis is the patient. The randomization of FPs will be achieved using the treatment assignment module of Epidat® 4.1; the proposed intervention will be considered the treatment, and usual care will be considered the control. To guarantee an equal number of FPs in each group (intervention and control), the option “balanced groups” will be selected. Once all participating FPs have selected their patients and have collected the corresponding initial data, the Research Unit, Primary Care Management of Madrid, will randomize them centrally. Subsequently, each FP will receive the information of the study group to which they have been assigned, at which time all the patients they have recruited will be included in that group.

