### Variables

FPs will provide their data before the start of the study. Patient data will be collected by the recruiting FP, who will also be responsible for patient follow-up. All information will be recorded in a case report form designed for the study. Each FP will access the form from their personal computer through the project website using a personal identification code. Four visits were defined for patient data collection: baseline (T0), 6 months (T1), 12 months (T2), and 18 months (T3) (see Table 1).

**Table 1 Tab1:** Visit plan

	T0 (baseline)		T1 (6 m*)	T2 (12 m*)	T3 (18 m*)	Responsible entity
Confirm inclusion/exclusion criteria	X					FP
Written informed consent	X					FP
Sociodemographic variables	X					FP
Morbidity variables and drug treatment plan	X		X	X	X	FP
Randomization of FP´s		X				RU
FP intervention (intervention group)		X				RT
Patient intervention (intervention group)			X	X	X	FP
Mortality				X	X	RT/FP
Hospitalizations				X	X	RT/FP
Functionality (WHODAS), falls, hip fractures			X	X	X	FP
Use of health services			X	X	X	RT
Quality of life	X			X	X	FP
Usability, adhesion, satisfaction			X		X	TG
Costs					X	RT

*T* time, *FP* family physician, *RU* research unit, *IG* intervention group, *RT* research team, *TG* technical group, *m** months from randomization

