## Trial status

Protocol Version Rev.0 (19.03.2019) + Anexo 2 Rev.0 (05.04.2019). Recruitment started on February 27, 2020. Approximate date for end of recruitment February 28, 2022.

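### Eligibility is formally checked only at T0, but allocation comes months to over two years later and takes in every recruited patient, with no check just before randomisation

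*Protocol article*

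**What the plan says.** **When eligibility is checked.** Under Recruitment, the FP is to "confirm the inclusion/exclusion criteria and obtain the patient’s written informed consent" once a patient agrees to take part. In Table 1 (Variables), the row "Confirm inclusion/exclusion criteria" is marked at T0 only. Randomisation of FPs stands in a separate, later column.

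**Who is allocated, and when.** Under Randomization, central randomisation takes place after all participating FPs have selected their patients and entered the initial data. Each FP is then told the assigned group, "at which time all the patients they have recruited will be included in that group". No exception is given. The Table 1 footnote counts the follow-up visits in months from randomisation.

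**Dates.** The Recruitment section (text below the Fig. 1 caption) says: "The recruitment of patients began in November 2019 and was suspended in March 2020". It adds that "it was not possible to restart the study until May 2021", and that in that month the FPs' situation was reviewed, "as well as the situation of the patients recruited between November 2019 and February 2020". Trial status gives a different start, "Recruitment started on February 27, 2020", and "Approximate date for end of recruitment February 28, 2022".

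**The concern.** Several criteria under Study population describe a state that can change: five or more drugs over the preceding three months, contact with the FP in the last year, not living in an institution, ability to follow the study, and a life expectancy that the doctor does not put below 12 months. They are verified at consent, but the comparison starts at randomisation. The inclusion rule is a positive statement covering every recruited patient, so it does more than leave a detail open.

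A patient who has died, been institutionalised or come off polypharmacy between the two dates has little or no scope to benefit from a prescribing intervention. Under intention to treat, such patients pull the two arms together on hospital admission or death. The article also does not say how a death or admission between T0 and randomisation is treated.

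The timing of any correction matters because FPs and patients are unblinded (Blinding). Removing patients before allocation is known cannot favour an arm, whereas removing them afterwards could.

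**Working it through.** **1. The plan's own figure.** Inputs from Sample size: 16% and a difference of six points (so 16% versus 10%), 80% power, 5% alpha (taken as two-sided), simple random sampling. With pooled variance under the null and p̄ = 0.13:

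n per arm = [1.960·√(2·0.13·0.87) + 0.842·√(0.16·0.84 + 0.10·0.90)]² / 0.06² = 492.0

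This gives 492 per arm and 984 in total, as stated.

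**2. Waiting times.** Inputs: the dates in Recruitment and Trial status. I assume randomisation directly after the planned end of recruitment, 28 February 2022; a later date lengthens every interval.

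| From | Months to 28 Feb 2022 |
|---|---|
| 1 to 30 November 2019 (Recruitment) | 27.9 to 27.0 |
| 27 February 2020 (Trial status) | 24.0 |
| 1 to 31 May 2021 (restart and review) | 10.0 to 9.0 |

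The longest wait is about 28 months on one start date and 24 on the other. Only patients recruited before the suspension can wait this long. They were the ones reviewed in May 2021, 14 to 19 months after recruitment. From that review, or from recruitment after the restart, the unchecked interval is at most about 9 to 10 months.

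**3. Deaths in the unchecked interval.** The documents give no mortality rate. I assume h = 1% to 3% a year and use 1 − (1 − h)^(months/12).

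| h per year | 9 months | 10 months |
|---|---|---|
| 1% | 0.75% | 0.83% |
| 2% | 1.5% | 1.7% |
| 3% | 2.3% | 2.5% |

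The range is about 0.8% to 2.5%. It applies the longest post-restart wait to every patient, so for patients recruited later it is an upper figure. It leaves out institutionalisation and loss of polypharmacy, for which the article has no rates.

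**4. Effect on power.** If a fraction f of each arm cannot benefit and keeps the control risk, the intervention rate becomes 10 + 6f per cent and the difference 6(1 − f) points. With n = 492 per arm and d the difference:

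power = Φ{[d·√n − 1.960·√(2p̄(1−p̄))] / √(p₁(1−p₁) + p₂(1−p₂))}

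| f | Intervention rate | Difference (points) | Power |
|---|---|---|---|
| 0 | 10.00% | 6.00 | 80.0% |
| 0.8% | 10.05% | 5.95 | 79.3% |
| 2.5% | 10.15% | 5.85 | 77.8% |

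**The case against.** There is a good case that this is minor.

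- *The longest-waiting patients were looked at again.* The May 2021 review covers the cohort with the 24 to 28 month wait. A reader might infer that patients long dead or ineligible are certainly in the trial, and size the problem on the full 28 months. The documents do not support that, because the review may have removed them. What stands is that the article names neither the criteria applied nor the action taken, and that the review lies 9 to 10 months before the planned end of recruitment.
- *The details may be elsewhere.* Fig. 1 and the additional file on pandemic modifications are not shown and may report what the review led to. That limits any complaint about missing detail. It does not alter the inclusion rule under Randomization or the single T0 mark in Table 1.
- *A later change is not ineligibility.* The drug criterion is tied to inclusion, and a patient enrolled at 73 who turns 75 was validly included. This stands. Nor does a 12-month life-expectancy exclusion contradict an 18-month endpoint.
- *The dilution could be exaggerated.* A reader might infer power of about 75% or 70%. That needs 5% or 10% of the whole trial to be without possible benefit, and nothing in the article supports such fractions. The 8% loss allowance might also absorb some of these patients.
- *Early deaths may already fall outside the endpoint.* The primary outcome refers to the observation period, and visits run from randomisation, so on a natural reading a death before randomisation is not an event. The text does not say so, and such a patient would still be allocated.
- *Recruiting before randomisation is a protection.* It prevents FPs from choosing patients once they know their arm (Discussion). That is right, and a check made before allocation keeps that protection intact.

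**Conclusion.** The point holds in a limited form. The article verifies eligibility at T0, allocates after all recruitment is complete, and takes every recruited patient into the arm with no check at randomisation. Read literally, it allocates patients who have died, been institutionalised or lost polypharmacy in the interval. The part of the interval with no reported check is about 9 to 10 months. The full wait of 24 to 28 months applies only to early recruits, whose situation was reviewed in May 2021 with no stated outcome.

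The statistical cost is small, a loss of roughly one to two percentage points of power. It rests on an assumed mortality of 1–3% a year, on randomisation immediately after 28 February 2022, and on no benefit for those patients. Institutionalisation and loss of polypharmacy would add to it by an amount the documents do not allow one to estimate. The change is still worth making, because it is cheap and can be made without risk of bias only before allocation is known.

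**What to change.** 1. In Randomization and in Table 1, add a brief reconfirmation by each FP, immediately before central randomisation and while allocation is unknown, of vital status and continued eligibility under the protocol's own criteria. Passing age 74 after valid consent should not count as a failure, and the age criterion needs no change.
2. List patients who fail as pre-randomisation exclusions in the flow diagram and do not allocate them.
3. State that primary outcome events count only from randomisation.
4. State what the May 2021 review checked and what followed from it, and reconcile the start of recruitment given in Recruitment (November 2019) with that in Trial status (27 February 2020).

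The cost is a short record check per patient and a small loss from the nominal sample size. The comparison is not biased, because nobody knows the allocation when the check is made.

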### Intervention

This is a complex intervention that includes the training of FPs and physician-patient interview based on the Ariadne principles; the effectiveness of the intervention has been studied in the MULTIPAP RCT [23, 36, 37]. The training includes activities related to basic concepts of multimorbidity, the appropriateness of prescriptions, adherence to treatment, the ARIADNE principles, and shared doctor-patient decision-making. All participating physicians will receive this training with the objective of incorporating patient-centred interviews into their routine clinical practice. This would allow the effect of the training to be isolated from the use of a DSS.

